**Fig. 2 Fig2:**
[figure not shown]
Screenshot of MIND-VR: map of the three paths into which the virtual island is divided: (1) “An introduction on stress and anxiety,” (2) “Causes and symptoms,” and (3) “Main treatments.” Participants in the experimental group will try the first path during the first training session, the second path during the second training session, and the third one during the third training session

#### Control group

This group will undergo baseline, post-intervention, and follow-up assessments without undergoing any training during the 1-week intervention period.

### Virtual reality experiences

#### Virtual reality psychoeducational experience on stress and anxiety: MIND-VR

MIND-VR is a VR-based psychoeducational experience on stress and anxiety created by a team from the University of Milano-Bicocca, thanks to the funds raised through a crowdfunding campaign [50]. This virtual experience was developed in collaboration with AnotheReality between July and October 2020 using Unity Engine. MIND-VR runs on one of the currently more widespread, user-friendly, and low-cost HMDs (i.e., Oculus Quest 2), and it can be downloaded for free, both in Italian and English, on the project website (https://mindvr.com/free-download/).

This VR-based psychoeducational experience has been created following the theoretical framework of architectural approaches for the user-centered design (UCD) of virtual environments developed by Gladden [70]. Since the scientific literature suggests that naturalistic virtual environments cause a relaxing effect and an increase in positive emotions [71–73], a small tropical island was chosen as the setting. The virtual island is divided into three areas. Each focused on different aspects related to stress and anxiety and presented to the user through a map at the beginning of the content (Fig. 2). In each area, the users, as if they were inside a museum, can follow a path along which they will find information in text, audio, and image form on the definitions (first path), causes and symptoms (second path), and main treatments (third path) of stress and anxiety. Each of the routes takes about 15 min to be ended.

#### Relaxing virtual experience: The Secret Garden

The Secret Garden is a 10-min computer graphic 360° video developed by [name] and colleagues [26, 64] for relaxation training and freely available at the website www.covidfeelgood.com. Well-being psychologists have written this experience to mimic the structure and the experience of walking in a Japanese garden [74], providing the visual (i.e., the flow of water) and auditory (i.e., the sound of running water) natural elements available outdoors (Fig. 3).

**Fig. 3 Fig3:**
[figure not shown]
Screenshot of The Secret Garden

During The Secret Garden, a slow, calm, clear voice provides a relaxation induction based on Compassion Focused Therapy (CFT) [75, 76]. Specifically, the induction aims to deactivate the human threat protection system and activate the soothing system (with a mindset attended to giving and receiving care, affecting, and nurturance).

#### Hardware

The virtual experiences will be offered through the Oculus Quest 2 (marketed since November 2021 as Meta Quest 2). It was released in October 2020 and is a standalone headset with an internal, Android-based operating system. It is lighter than the first-generation Quest and uses a single fast-switch LCD panel with 1832 × 1920 per eye resolution, and it supports a 90-Hz refresh rate.

### Outcomes

#### Primary outcome measure

At baseline, post-intervention, and follow-up, participants in the experimental and in the control group will complete the following questionnaires that will serve as the primary outcome measures:*Perceived Stress Scale* (PSS-10) [77, 78]: the PSS is a 10-item self-reported measure to assess the current stress level using a 5-point Likert scale.*State-Trait Anxiety Inventory Form Y-2 (STAI-Y2)* [79, 80]: a validated and widely used measure of trait anxiety. Individuals are asked to specify to which extent, on a 4-point Likert scale (from “not at all” to “very much”), they usually perceive each of the 20 indicated feelings.*The Depression, Anxiety and Stress Scale-21 Items (DASS-21)* [81]: is a set of three self-report scales designed to measure depression, anxiety, and stress symptoms. Each of the three scales contains seven items, divided into subscales with similar content. The scores for depression, anxiety, and stress are calculated by adding up the scores for the relevant items.Ad hoc* questionnaire on the knowledge of stress and anxiety*: individuals are asked to rate on a 7-point Likert scale (1 = “not at all,” 7 = “very much”) knowledge about the differences between anxiety and stress, causes and symptoms of stress and anxiety, and techniques for the management of these conditions. Besides, participants complete 5 factual questions in multiple-choice format (e.g., “Which is the first phase of the General Adaptation Syndrome?”) and 2 conceptual questions in short-answer format (e.g., “What are the three main categories of stress symptoms?”). The questions are based on the methodology used in a previous study (Parong and Mayer, 2018) (see Table 4).

**Table 4 Tab4:** The ad hoc questionnaire on the knowledge of stress and anxiety

Questionnaire on the knowledge of stress and anxiety
***Part 1. Rate on a 7-point Likert scale (1***** = *****“not at all,” 7***** = *****“very much”) your level of knowledge about*****:** • The differences between anxiety and stress • Causes and symptoms of stress and anxiety • Techniques for the management of stress and anxiety
***Part 2. Answer the following questions*****:** • What is the first stage of the “general stress adaptation syndrome”? -Resistance phase -Exhaustion phase -Alarm phase -None of these • What is the main difference between stress and anxiety? -Symptoms and duration -Duration and causes -The causes and duration • Which of these is a symptom of social anxiety? -Constant and pervasive anxiety -Avoidance of social situations -Fear of enclosed spaces -None of the above • What is the main difference between acute stress disorder and post-traumatic stress disorder? -Duration -The causes -None of the above • Which of these biofeedback claims is incorrect? -Its primary purpose is to teach how to modify physiological response patterns -It consists of several sessions -Focuses on breathing -None of the above
***Part 3. Open-ended questions*****:** • What are the three main categories of stress symptoms? • What are the main techniques for the management of stress and anxiety?

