### Objectives

The primary objective of this RCT focus on the usefulness of the proposed home-based VR intervention for decreasing stress and anxiety and for enhancing the knowledge about these conditions compared to a control group. The secondary objective is to assess the acceptability of the home-based VR training.

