### Sample size

Power size calculation was performed with GPower 3.1. Considering an anticipated effect size (*f*) of.25, an alpha set at 0.05, 2 groups, and a 0.95 statistical power, the total sample size required is *N* = 54. We, therefore, plan to enroll a total of 60 participants, which should guarantee a proper sample even in case of drop-outs.

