### Data analysis

Analysis of variance will be used to evaluate baseline characteristics of the two groups involved in the study, the overall significance of improvement across primary outcome measures, and drop-out versus maintainers. Categorical variables will be compared using Fisher or chi-square tests and continuous variables using *t*-test or Mann–Whitney tests, as appropriate. To assess the effectiveness of the intervention, groups will be compared with a 2 × 2 repeated measure mixed ANOVA for the pre- and post-primary outcome measures (factor Group X factor Time: pre and post). The analysis will be performed for the PSS, STAY-Y2, and DASS-21. A repeated-measures ANOVA (factor Group × factor Time: day of the week) will compare treatment effects within the 1-week intervention for the STAY-Y2 and the VAS-A. Tests of statistical significance and confidence intervals will be two-sided. A *p* < 0.05 will be considered statistically significant. Descriptive methods will be used to report the usability of the intervention for the secondary outcome intervention (i.e., SUS, SDM, NPS, ad hoc questionnaire on difficulties and adverse effects). Data analyses will be carried out through SPSS software.

Recordings from the post-intervention interviews will be transcribed. Two researchers will read the interview transcripts carefully several times to have a sense of the whole data, identifying emerging themes and categories [87]. A codebook will be created and modified until the final set of codes is obtained and reached to the data saturation point when there is no emergence of other new themes. Qualitative data analysis will be conducted using a thematic content analysis approach following a systematic process. Codes will be applied to the transcripts and converted into categories to represent the main themes arising from the data [88]. Triangulation of themes and concepts will be used to compare further and contrast the data from the different participating groups. Codes will be applied to the transcripts and converted into categories to represent the main themes arising from the data [88].

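### One of the five multiple-choice knowledge items is printed with two options that mean the same thing, so it offers two distinct answers rather than three

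*Protocol article*

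**What the plan says.** The Objectives section makes knowledge part of the primary objective: the training is meant to help in "enhancing the knowledge about these conditions compared to a control group". Under Primary outcome measure, the ad hoc knowledge questionnaire is one of four "questionnaires that will serve as the primary outcome measures", beside the PSS-10, STAI-Y2 and DASS-21. Both arms complete it at baseline, post-intervention and follow-up.

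The questionnaire has three self-ratings, a multiple-choice part and two open questions. On the multiple-choice part the article says that "participants complete 5 factual questions in multiple-choice format". Table 4, Part 2 prints all five items with their options. The second reads "What is the main difference between stress and anxiety? -Symptoms and duration -Duration and causes -The causes and duration".

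The article gives no key or scoring rule for Part 2. It says only: "The questions are based on the methodology used in a previous study".

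**The concern.** Call the three printed options A, B and C, in order. B and C name the same two concepts and differ only in word order and an article. A participant who holds that view has no basis for choosing between them, and a participant who assumes a single correct answer may reject both. None of the other four items repeats an option.

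This is a fault in the instrument as printed, not a detail left to another document. A scoring rule can limit the damage afterwards, but it cannot change what participants were shown. At stake is how well one fifth of the multiple-choice items separates people who learned the content from people who did not. If the VR arm learns more, as the trial hypothesises, weaker discrimination would shrink the between-arm difference on this item.

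**Working it through.** **Figures in the plan.** The article attaches no number to this item. Its sample size ("an alpha set at 0.05, 2 groups, and a 0.95 statistical power, the total sample size required is" 54) is not affected. It reproduces as a two-group, two-time-point interaction with f = 0.25 and an assumed correlation of 0.5: power is 0.9501 at N = 54.

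**Inputs from Table 4.** The five items have 4, 3, 4, 3 and 4 printed options. The item in question is the second, with 3.

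**Assumptions (not in the article).** Participants who do not know guess evenly among the printed options. Those who know choose correctly, except that when B and C are the right content a share *s* picks the uncredited wording. The five items have equal weight.

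**Measure.** Discrimination D = P(credited | knows) − P(credited | guesses). The expected between-arm difference on an item is D times the difference in the share who know.

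**The item under each possible key**

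- Three distinct options: D = 1 − 1/3 = 0.67.
- Only B or only C credited: D = (1 − *s*) − 1/3.
  - *s* = 0: D = 0.67, no loss.
  - *s* = 0.5: D = 1/2 − 1/3 = 0.17, a loss of 0.50. A fully informed participant then expects 4.5 of 5.
  - *s* = 1: D = −0.33. D is negative once *s* exceeds 2/3.
- Both B and C credited: D = 1 − 2/3 = 0.33, a loss of 0.33. No one who knows is marked wrong.
- A credited: D stays at 0.67 if no one reasons from the duplication. It falls to 1 − 1 = 0 if everyone who does not know eliminates B and C.

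**The five-item part**

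- Total signal with sound items: 3 × (1 − 1/4) + 2 × (1 − 1/3) = 2.25 + 1.33 = 3.58.
- One wording credited, *s* = 0.5: 0.50 / 3.58 = 14% lost. Over *s* from 0 to 1 the loss is *s* / 3.58, that is 0% to 28%.
- Both credited: 0.33 / 3.58 = 9% lost.

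**Illustration.** Suppose true knowledge is 30% in one arm and 80% in the other (assumed). The expected item difference is 0.50 × 0.67 = 0.33 with a sound item, 0.50 × 0.17 = 0.08 with one wording credited and an even split, and 0.50 × 0.33 = 0.17 with both credited.

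**The case against.** The strongest reply is that the harm depends on a key the article does not show, and an article may properly leave a key to the full protocol. If both wordings are credited, no informed participant loses a mark. That stands. A reader might infer that correct participants are being marked wrong, or that the item fails however it is scored. The documents support neither: the first needs B and C to be the right content with only one wording credited, and the second overlooks crediting both.

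A reader might also take the fall from 0.67 to 0.17, a 75% loss, as the size of the problem. It describes one item at an assumed even split. The score-level figures are smaller, and even they presume an equally weighted five-item sum that the article does not define. The self-ratings and open questions are untouched.

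The duplication may exist only in the English table. Participants are Italian healthcare workers and the article has other copying slips. This is possible, and the documents do not settle it, which is why the administered form must be checked first. It does not make the printed item sound.

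The effect on the trial's conclusions is limited. For the 2 × 2 mixed ANOVA the Data analysis section says: "The analysis will be performed for the PSS, STAY-Y2, and DASS-21". Knowledge is not named. The same section does plan an ANOVA of improvement across the primary outcome measures, so knowledge is not outside the analysis altogether.

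Two further inferences go too far. That the error falls mainly on the VR arm is plausible, but baseline knowledge is not given and healthcare workers may already know the answer. That the item tests the central lesson of the first VR path is not stated: that path covers definitions, while causes and symptoms belong to the second.

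**Conclusion.** The point holds for the item as printed: two of its three options are equivalent, in a questionnaire that is a listed primary outcome. Under even guessing and equal weights the multiple-choice part loses about 9% of its signal if both wordings are credited. If only one is credited it loses about 14% at an even split, within a range of 0% to 28%. If the first option is keyed, the loss depends on how many participants reason by elimination, which cannot be known from the article.

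The effect is confined to one of five multiple-choice items in one of four primary measures. It does not touch the sample size or the stress and anxiety outcomes, and it does not invalidate the knowledge outcome as a whole. Whether participants actually saw the duplication is open.

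**What to change.** 1. Check the Italian form as administered. If the duplication is only in the published table, correct the table; nothing else is needed.
2. If it is in the form, treat the two equivalent wordings as one answer: both credited or both not. Fix the key before group labels are attached to the data.
3. Report the knowledge result with and without this item, using the other four items for the second version. This also covers the case where the first option is keyed, which identical scoring does not cure.
4. Optionally, replace one duplicate with a distinct distractor for participants not yet at baseline. Recruitment was ongoing at submission, and the Protocol amendments section gives the route through the ethics committees.

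Steps 1 to 3 cost one check, one scoring rule and one extra analysis. Step 4 creates two versions of a primary instrument with different guessing rates (if both wordings are credited, 2/3 on the old form against 1/3 on the new), so it is secondary to the scoring fix. The four-item result would be the common measure across versions.

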#### Secondary outcome measure

Participants in the experimental group at post-intervention will complete the following questionnaires that will serve as the secondary outcome measures: *System Usability Score (SUS) *[82]*:* it consists of 10 items on a 5-point Likert scale (1= “strongly agree,” 5= “strongly disagree”), relating to the possible critical issues encountered during the use of a VR system. A measure is provided on usability aspects (i.e., efficiency, clarity, reliability) and other aspects of the user experience (i.e., originality, stimulation).*Subjective Difficulty Measure (SDM):* it consists of a horizontal line 100 mm long, anchored by word descriptors at each end (from “not at all” to “very much”). Users mark on the line the perceived difficulty in using the VR system in general, MIND-VR, and The Secret Garden.*Net Promoter Score (NPS) *[83]: it evaluates user satisfaction with a product, in this case: the VR-home-based intervention in general, MIND-V, and The Secret Garden. It requires to indicate on a scale from 0 (“not at all”) to 100 (“very much”) how much they would recommend the products to a family member or friend.*Ad hoc questionnaire on difficulties and adverse effects*: individuals are asked to rate on a 7-point Likert scale (1=“not at all,” 7 = “very much”): If they had difficulty following the experimental protocol; if they had nausea, headache, dizziness, and eyestrain while using the VR system in general; if they had nausea, headache, dizziness, and eyestrain while using MIND-VR; if they had nausea, headache, dizziness, and eyestrain experienced while using The Secret Garden.

Furthermore, adherence to study protocols will be assessed through data on VR usage recorded on the log book, training sessions completed, assessments attended, and drop-outs. Data recorded by participants on the log book regarding technical problems and safety issues will serve to evaluate the usability of the VR system.

Finally, during the post-training session, participants of the experimental group will be interviewed for about 15 min. The questions will be based on the methodology used in a recent study [51]: Were there any features that you especially liked in using the home-based VR training? Were there any features you did not like or found useless? Have you ever had to stop using VR, and if so, why? Have you learned anything using MIND-VR and The Secret Garden? Were there any features of the VR experiences more valuable than others? Would you like to have more sessions with this type of training? Do you have any questions or would like to add anything?

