### Withdrawn criteria

Participants will be considered withdrawn if any of the following occurs: (1) participant chooses to withdraw from the study at any time, (2) intolerable adverse effects, (3) major violation of the study protocol, and (4) other circumstances that would endanger the health of the subject if he/she were to continue his/her participation in the trial. The date and reason for withdrawal will be documented in a paper-and-pencil case report form (CRF).

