#### Experimental group

Participants in the experimental group will receive the home-based VR intervention. Following a description of the protocol in detail:*Intake session (session 1):* after signing the informed consent and completing the baseline questionnaire accessible online (i.e., demographic, ad hoc questionnaire about the use of technological solutions and VR, ad hoc questionnaire on the level of exposure to COVID-19, FCOR, ad hoc questionnaire on stress and anxiety management, PSS-10, STAI-Y2, DASS-21, ad hoc questionnaire on knowledge of stress and anxiety), participants will receive from the research psychologist an explanation about the aims and methods of the home-based VR program. Participants will be asked for their involvement and availability during a week to allow in-home training. The psychologist will remind participants to perform the training three per week, with a distance of 2 days between one session and another. Then, individuals will receive information about the safety and hygiene procedures to prevent COVID-19 infection (see Table 3). The psychologist will give participants the Oculus Quest 2, a consumer-grade standalone VR system that consists of an HMD and two controllers. Individuals will wear the headset and receive a short 15-min training on using the VR system. In particular, they will try the tutorial content available on the Oculus Store. Furthermore, individuals will receive a link to complete the online questionnaires (i.e., STAI-Y1, VAS-A) before and after each session. They will be provided with a log book in which to record technical problems, safety issues, and the date and time they used VR during the intervention. Finally, the research psychologist will schedule the date of the post-training session.*Training sessions (sessions 2, 3, and 4):* they will consist of three home sessions of approximately 30 min each, conducted in a week with a distance of 2 days between one session and another. Participants will try for about 15 min one path of the virtual psychoeducational experience MIND-VR in each session (see Fig. 2). Subsequently, they will use for about 10 min the virtual relaxation content The Secret Garden. Individuals will be asked to complete online the VAS-A and the STAI-Y1 at the beginning and the end of each session.*Post-training session (session 5):* the research psychologist will meet participants for the post-intervention interview at the end of the training. On this occasion, participants will return the Oculus Quest 2, which will undergo specific procedures to avoid contamination by COVID-19. Participants will be asked to complete within 1 week after completion of the intervention the online questionnaires (i.e., PSS-10, STAI-Y2, DASS-21, ad hoc questionnaire on knowledge of stress and anxiety, SUS, SDM, NPS, ad hoc questionnaire on difficulties and adverse effects).*Follow-up session (session 6):* the PSS-10, STAI-Y2, DASS-21, and the ad hoc questionnaire on knowledge of stress and anxiety will be conducted after a 1-month follow-up.

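### The acceptability ratings are scheduled once, at post-intervention, and none is described for participants withdrawn early, so their summaries may lean towards those who tolerated the training

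*Protocol article*

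**What the plan says.** The Objectives section makes acceptability of the home-based training the secondary objective. The Secondary outcome measure section lists the System Usability Score (SUS), the Subjective Difficulty Measure (SDM), the Net Promoter Score (NPS) and an ad hoc questionnaire on difficulties and adverse effects, and times them all together: "Participants in the experimental group at post-intervention will complete the following questionnaires that will serve as the secondary outcome measures". Table 2 agrees. Each of the four, and the interview, has a single mark in the post-intervention column at week 1.

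The Experimental group section sets the window: "Participants will be asked to complete within 1 week after completion of the intervention the online questionnaires".

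The Withdrawn criteria section lists, beside the participant's own choice, "2) intolerable adverse effects". For a withdrawn participant it asks that the date and the reason be entered on the case report form (CRF). It mentions no exit questionnaire.

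The Data analysis section says: "Descriptive methods will be used to report the usability of the intervention for the secondary outcome intervention". It gives no rule for people who stopped early.

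Other information on leavers is collected. The Secondary outcome measure section also states that "adherence to study protocols will be assessed through data on VR usage recorded on the log book, training sessions completed, assessments attended, and drop-outs" and that "Data recorded by participants on the log book regarding technical problems and safety issues will serve to evaluate the usability of the VR system". The Data management section puts any adverse event on the CRF.

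**The concern.** Some of the events that can take a person out of the study are the events that the scales measure. Nausea and dizziness are items on the adverse-effects questionnaire. Intolerable adverse effects are a ground for withdrawal, and the Ancillary and post-trial care section says that nausea or vertigo reported during the intervention could lead to stopping. If the ratings are obtained only at the end, whether a rating exists depends on the quantity being rated. The likely direction is favourable to the product: usability and recommendation too high, difficulty and symptoms too low.

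At stake is the reading of the whole secondary objective. The abstract and the Discussion look ahead to a training that is easy to use and can be put into practice quickly. With 30 people in the experimental arm, a few unrated leavers can move a descriptive mean.

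**Working it through.** **Step 1. Does the schedule reach an early leaver?**

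| Source of information | Reaches someone withdrawn early? | Supplies the scale ratings? |
|---|---|---|
| SUS, SDM, NPS, adverse-effects questionnaire (post-intervention) | Not described | Yes, if given |
| Interview at the post-training session, including the question on having had to stop VR | Not described | No, but gives the reasons in the person's own words |
| Log book, sessions completed, drop-outs | Yes | No |
| Withdrawal date and reason; adverse events on the CRF | Yes | No |
| Phone call to those who miss questionnaires or the post-training session | Not stated for a withdrawn person | Only indirectly |
| Drop-outs compared with maintainers | Yes | No; it cannot compare ratings never collected |

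The gap is therefore confined to the ratings and the interview of people withdrawn early.

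**Step 2. What loss does the plan allow for?** The Sample size section gives 54 required and 60 enrolled. The 54 reproduces for the 2 × 2 group-by-time interaction with f = 0.25 and alpha 0.05, if the pre-post correlation is taken as 0.5 (my assumption; the article does not give it). The noncentrality is 0.25² × 54 × 2 / (1 − 0.5) = 13.5 on 1 and 52 degrees of freedom, and the power is 0.950. The allowance is 1 − 54/60 = 10%, or 0.10 × 30 = 3 people in the experimental arm. It covers drop-out for any reason, so 3 stopping for poor tolerance is an illustration and not a forecast.

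**Step 3. How far could a mean move?** Let d of the 30 starters be unrated. Then

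completer mean − mean over all starters = (d/30) × (completer mean − leaver mean).

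Assume a completer mean SUS of 80, leavers who would have scored 30 to 50, and scoring from 0 to 100. The article gives only ten five-point items, so the scoring range is also an assumption.

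| d | Leavers at 30 | Leavers at 50 |
|---|---|---|
| 1 | (29 × 80 + 1 × 30)/30 = 78.3 | (29 × 80 + 1 × 50)/30 = 79.0 |
| 3 | (27 × 80 + 3 × 30)/30 = 75.0 | (27 × 80 + 3 × 50)/30 = 77.0 |
| 6 | (24 × 80 + 6 × 30)/30 = 70.0 | (24 × 80 + 6 × 50)/30 = 74.0 |

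**Step 4. Upper bound.** With d = 3, the most that a mean can shift is 3/30 × 100 = 10 points on a 0 to 100 scale (the SDM line and the NPS rating) and 3/30 × 6 = 0.6 on the 1 to 7 symptom ratings.

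**The case against.** A reader might infer that people who stop VR never contribute, and that the acceptability result is simply a completers' result. The document does not support that. The same outcome section uses sessions completed, drop-outs and log-book entries, and those entries are made while the training is under way. Withdrawal reasons and adverse events go on the CRF.

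Stopping VR is also not the same as withdrawing from the study. The outcome section addresses the experimental group at post-intervention and does not require three sessions. The date of the post-training session is fixed at intake. The adherence section has the psychologist phone anyone who misses the questionnaires or that session, and the interview asks about having had to stop. Someone who stops VR but stays in the study is not barred. The wording on completion of the intervention can be read as a response window and not as an eligibility rule. All of this stands, and it narrows the point to people withdrawn early.

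It can also be said that an article may leave exit procedures to the full protocol. That has some force, and an exit visit may exist there. But the point rests on a schedule that this article itself states in three places, and that schedule includes no early-stop collection of these ratings.

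Finally, these outcomes are secondary and descriptive, no test depends on them, and some leavers will decline further forms. That bears on how much weight the point deserves. It does not remove it, because none of the other sources supplies the ratings that the Data analysis section will summarise.

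**Conclusion.** The point holds in a limited form. The four questionnaires and the interview have one stated administration, and none is described for participants withdrawn early, including for intolerable adverse effects. Their summaries may therefore cover mainly those who tolerated the training and be biased towards good acceptability.

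The size cannot be fixed from the document, because it gives neither a stop rate nor leavers' scores. Under the assumptions above, 3 unrated leavers turn a completer mean SUS of 80 into about 75 to 77 over all starters; 1 leaver gives 78.3 to 79.0 and 6 give 70 to 74. A reader might go further and calculate a changed net promoter score or a changed rate of marked nausea. The article defines no promoter or detractor cut-offs and no threshold on the 1 to 7 rating, so such figures have no basis in it.

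This is a cheap improvement to descriptive secondary outcomes. The primary analysis and the sample size are not affected.

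**What to change.** **Collection.** In the Experimental group section, the Secondary outcome measure section and Table 2, state that SUS, SDM, NPS, the difficulties/adverse-effects questionnaire and the short interview are offered to every experimental participant who used the headset at least once. Do this when VR is stopped or the headset is returned, whichever is first, regardless of the number of sessions done. The intake session includes a headset tutorial, so some leavers may have tried only part of the content. Record items about content not tried as not applicable.

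**Reporting.** In the Data analysis section, report each rating with the number who started VR as the denominator and with the number missing. Show completers separately. Present withdrawals for adverse effects beside the symptom ratings and do not merge them in, because one is an event count and the other a rating.

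**Cost.** Wording in a few places and a few extra contacts. The online forms and interview questions already exist, and the headset has to come back in any case. Some leavers may decline, so the gap will shrink but may not close. The acceptability figures may look slightly less favourable.
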